### Sample size

The study sample will comprise 600 mother-infant dyads, with 200 eligible pairs each assigned to one of the three study conditions. Using the software Optimal Design (Version 3.01) [64], we determined that a sample of 600 participants will lend our study adequate statistical power which allows us to observe an effect from the study interventions. Using the repeated measures module of the software under the setting of a cluster randomized trial with person-level outcomes and assuming an intraclass correlation coefficient (ICC) of 0.7, we found that the study will have a statistical power of 0.80 to detect an effect size of 0.338, which is slightly above the small effect size defined by Cohen’s d. The ICC of 0.7 is typical for individual’s serial correlation found from most longitudinal studies. If the ICC is reduced to 0.3, the study can detect an even smaller effect size of 0.31.

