During the information sessions, the study coordinator will review and provide a full description of the study including information about the mothers’ obligations, surveys, and child nutrition and development measures. Once eligibility is established, study participants will go through the informed consent process individually. The study staff will provide the mothers with a verbal description of the study, which will explain the purpose of the study, their role in the study, and what to expect during data collection. The risks and benefits of the study will be explained to the study participants, and we will obtain written consent. Mothers will be permitted the necessary time (up until the child ages out of eligibility) to consider entry into the study to allow for careful decision-making.

Enrollment and one year of follow up are to be completed within a four-year timeframe for five respective cohorts. There will be five staggered enrollments, where 120 caregiver-infant dyads are recruited in each six-month cycle, with 40 participating dyads in each of the three study arms. All participants will be compensated for transportation costs and lost work or market time during enrollment and child assessments.

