### Randomization

Using the website Randomization.com [65], we generated a list of randomization codes with a reproducible seed. These codes will be used to randomize the caregiver-infant pairs into one of the three study groups in a 1:1:1 ratio, with 200 dyads assigned to each study condition.

The randomization codes are set with 120 subjects randomized into eight blocks and with each block comprising 15 subjects. Within each block, each study arm is assigned five study subjects (Fig. 4). These 120 randomization codes will be used for each of the five enrollment cycles.

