#### Parenting intervention

Mothers randomized into the multicomponent *Grandi Byen* arm will simultaneously participate in the egg intervention and a psychoeducational parenting intervention conveying messages on nutrition, WASH practices, and responsive parenting. Originally developed and tested in Uganda [39], the group-based intervention was adapted and piloted in Cap-Haitien by the study team. The intervention is rooted in social learning theory and employs active and interactive learning strategies such as verbal instruction, modeling (vicarious experience), direct experience, and receiving feedback [69]. It is also based on cognitive, behavioral, and interpersonal therapeutic techniques that encourage shaping of knowledge, problem solving, practicing new behaviors and eliciting family social support [70, 71]. Messages are delivered and reinforced through a facilitated peer-group platform. The parenting intervention has 12 modules, emphasizing several key messages that emerged in our pilot work and are known to support healthy growth and development: maternal self-care, child development (stimulating play, interactive communication, and healthy families), complementary feeding with ASFs and continued breastfeeding, and household hygiene practices such as handwashing and use of soap. An adapted program manual guides each session. Table 2 details the 12 intervention modules for the *Grandi Byen* parenting program.

**Table 2 Tab2:** *Grandi Byen* parenting intervention modules

No	Title	Session summary/empirical support	Targeted mechanism
1	Parenting for strong, healthy children	Parental aspirations; challenges encountered; introduces mothers to five principles of healthy parenting covered in *Grandi Byen*: *hygiene, food, play, conversation, self-care*. **All 5 are reinforced in every session.**	Responsive parenting
2	Strong, healthy families 1	Common family stressors that can impact child development and ways to address them. Need for positive home environment to help young children to thrive; strategies to build positive mother-infant interactions.	Responsive parenting
3	Taking care of yourself	Mothers are taught to identify and link their emotions and behaviors. Positive strategies to deal with negative emotions are introduced.	

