4	Creating a stimulating environment for healthy development	Why young children need to play with objects in order to grow and learn; age-appropriate, readily available stimulating toys; mother-infant engagement	Responsive parenting
5	Talking and playing with children	New ways of talking to babies and why necessary; practice interacting with their child both verbally and non-verbally.	Responsive parenting
6	Animal source foods and diverse diets	What to feed and how much to feed infants/young children; continued breastfeeding; importance of diverse diets for young children, and why ASFs are critical in complementary feeding.	Nutrition^a^
7	Don’t forget the soap	Use of latrines and soap. Identifying barriers to handwashing and latrine use and how to overcome them.	WASH^a^
8	Positive family relationships	Strategies for positive communication and problem-solving skills for interpersonal conflict.	
9	Make play more challenging	Discusses why children need novelty and challenges. Identifies ways to make play more challenging. Identifies barriers to collecting new play things and strategies to overcome them.	Responsive parenting
10	Engaging with your children	Story-telling and other engaging activities (singing and dancing) are modeled by the facilitator and then practiced by mothers with their infants.	Responsive parenting
11	Strong, healthy families 2	This session builds upon earlier sessions focused on communication and family relationships and discusses ways to engage children’s father in play with their children. Mothers identify their own communication style and identity pros and cons of their style.	
12	Review session		

^a^Although only the primary focus of one session each, the importance of ASF and hygiene and sanitation will be reinforced weekly

Groups of 20 mother-child dyads will be formed based on location of residence in communities and will convene weekly in designated community sites (churches, schools, and community centers). Each session will last approximately one to two hours.

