### Statistical analyses

#### Primary and secondary outcomes

Inferential tests will be applied in the analyses for this trial. To determine differences across the three study arms, all analyses will follow an intention-to-treat framework. Moreover, all hypothesis testing will be based on a one-sided superiority paradigm because the analyses will examine whether the study interventions have beneficial impacts for the children in the study. A one-sided superiority framework is therefore legitimate, because by the theory of change for the development of the treatment program, the intervention’s positive impacts are predictable, and efforts will be made to minimize any unintended and undesirable side-effects. Specifically, the hypothesized sign for outcome variables has a positive sign, except for the child morbidities and infection, which we hypothesize to be reduced, thus indicated by a negative sign for the coefficient.

Descriptive statistics will be used to detail baseline socio-economic, demographic, and household characteristics of the study sample. Additionally, baseline and endline characteristics for the outcomes of interest will be presented in a table with means and standard deviations or medians with interquartile ranges for continuous variables and as percentages for categorical variables. Several variables represented in summary statistics will also be used as covariates in adjusted outcome analyses to ensure a convincible level of internal validity for key study variables such as the treatment effects. Additionally, covariates will be included in analyses based on the hypothesized pathways in Fig. 2 and will also be derived empirically. Empirically derived covariates will be included in analyses when a p-value < .1 results from the likelihood ratio test or the Wald test.

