The primary analytic model to test primary hypotheses of the primary study aims—aims 1 and 2 (Table 1)—is the growth curve analysis using hierarchical linear modeling (HLM) or hierarchical generalized linear modeling (HGLM), depending on whether the outcome variable is a normally distributed continuous variable or a categorical variable. In the current study, the different timepoints (i.e., five waves of data collection at baseline and 3-, 6-, 9-, and 12-month follow-ups) are nested within children. These clustering effects violate the independent-observation assumption embedded in a linear model, so we will use HLM (also known as a random-effect or mixed-effect model) to control for the nesting structure of the data. In this study sample, there is only one child per parent, thus the nesting effect of children within families is absent. We therefore plan to treat mother-child pairs as one study level. However, we apply a two-level HLM model that treats time as level 1 and children as level 2.

Aim 3 examines the pathways to child growth and development by testing a series of mediational effects of secondary outcomes: responsive parenting, child dietary diversity and nutrient intakes, biomarker status, allergies, bone maturation, acute diarrhea, and respiratory morbidity. To conduct HLM or HGLM analysis for this aim, we will employ the multilevel analysis specially developed for testing mediational effects [89]. The analysis will involve three models: a full model, a reduced model, and a model using the mediator as a dependent variable. For the time-to-event outcomes (diarrhea episode, respiratory infections, and allergies in first 6 months of follow-up), we will use a proportional hazards model [90, 91].

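### The primary two-level model leaves out the parenting groups in which arm 3 alone is treated, so arm 3 contrasts have standard errors that are too small if the group ICC exceeds zero

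*Protocol article*

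**What the plan says.** Dyads are randomised individually "into one of the three study groups in a 1:1:1 ratio" (Randomization), "with 200 eligible pairs each assigned to one of the three study conditions" (Sample size). Enrolment runs in five cycles of 120, "with 40 participating dyads in each of the three study arms" (Participant recruitment, eligibility, and screening).

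The parenting programme belongs to arm 3 only. Under Parenting intervention the article says: "Messages are delivered and reinforced through a facilitated peer-group platform". It adds: "Groups of 20 mother-child dyads will be formed based on location of residence in communities and will convene weekly in designated community sites". Arms 1 and 2 have no such groups.

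Under Statistical analyses, Primary and secondary outcomes, the growth-curve model for aims 1 and 2 is set out by level: "However, we apply a two-level HLM model that treats time as level 1 and children as level 2". The only other nesting discussed is child within family. As there is one child per parent, "thus the nesting effect of children within families is absent". The parenting group is not mentioned. In the same section, "all hypothesis testing will be based on a one-sided superiority paradigm"; no significance level is given.

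The Sample size section names a cluster-randomised software setting, but it explains its ICC of 0.7 as the serial correlation of an individual's repeated measurements.

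**The concern.** This is a partially nested design: children in arms 1 and 2 are treated one by one, while those in arm 3 are treated in groups. A facilitator who runs sessions well or badly, or a group that gels or does not, moves up to 20 children together. The article itself gives reasons to expect some shared effect. It relies on modelling, feedback and peer reinforcement, and its account of earlier parenting trials says that the relationship with the facilitator matters.

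A two-level model treats the 200 arm 3 children as 200 independent pieces of information. With positive group correlation there are fewer. The arm 3 contrasts then look more precise than they are, and a one-sided test errs in the direction that favours the intervention. Hypotheses 3 and 4, which carry the incremental-benefit question, rest on these contrasts. So do the confidence intervals that feed the economic sensitivity analysis for arm 3.

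**Working it through.** **Inputs from the article.** 200 dyads per arm; 40 per arm per cycle; five cycles; groups of m = 20 in arm 3; one-sided tests; detectable effect 0.338 at power 0.80 with a serial ICC of 0.7 (0.31 at 0.3); Hypothesis 4 effect size 0.36 on cognition.

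**Assumptions.** Alpha is 0.05 one-sided. The group ICC is 0 to 0.10. It means the part of the variance in a child's growth-curve summary that arises through the groups after randomisation.

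**The plan's own figure.** The mean-of-waves formula is (z_α + z_0.80) × √[(2/n)(ρ + (1−ρ)/T)]. With n = 200 and T = 5 it gives 0.217 (ρ = 0.7) and 0.165 (ρ = 0.3) one-sided, or 0.244 and 0.186 two-sided. With n = 100, two-sided, it gives 0.345 and 0.263. No standard variant tried reproduced 0.338 and 0.31 together. Since alpha and the module's variance inputs are not given, this does not show the figure to be wrong. The error-rate results below do not use it; the detectable effects do, and take it at face value.

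**Number of groups.** 40/20 = 2 per cycle; 2 × 5 = 10 in all.

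**Effect of omitting the group level.**

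- Design effect in arm 3: DE = 1 + (20 − 1) × ICC. In the comparator arm it is 1.
- True SE divided by two-level SE: F = √[(1 + DE)/2].
- Actual one-sided size: 1 − Φ(1.645/F).
- Detectable effect with the grouping allowed for (normal approximation): 0.338 × F.
- Power at 0.338: Φ(2.486/F − 1.645), where 2.486 = 1.645 + 0.842.

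| Group ICC (assumed) | DE | F | Actual size | Detectable effect | Power at 0.338 |
|---|---|---|---|---|---|
| 0 | 1.00 | 1.00 | 5.0% | 0.338 | 0.80 |
| 0.01 | 1.19 | 1.05 | 5.8% | 0.354 | 0.77 |
| 0.02 | 1.38 | 1.09 | 6.6% | 0.369 | 0.74 |
| 0.05 | 1.95 | 1.21 | 8.8% | 0.410 | 0.66 |
| 0.10 | 2.90 | 1.40 | 11.9% | 0.472 | 0.55 |

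Worked row, ICC 0.05: DE = 1 + 19 × 0.05 = 1.95; F = √(2.95/2) = 1.214; 1.645/1.214 = 1.355; upper tail 0.088.

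With Satterthwaite degrees of freedom (about 30 falling to 16 as the ICC goes from 0.01 to 0.10), the last four powers become 0.75, 0.72, 0.63 and 0.52. At a nominal 2.5% one-sided, the actual size runs from 3.1% (ICC 0.01) to 8.0% (ICC 0.10).

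**Where Hypothesis 4's 0.36 is passed.** (0.36/0.338)² = 1.134 = 1 + 19 × ICC/2, so ICC = 0.134 × 2/19 ≈ 0.014.

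**Simulation.** 20,000 trials per ICC were simulated, with one summary value per child in place of the full mixed model. Ignoring groups gave 4.9%, 5.3%, 6.6%, 9.0% and 11.8% in the order of the table. The 5.3% at ICC 0.01 was a low draw: 200,000 trials gave 5.8%. A group-aware test held 4.7 to 5.1% throughout.

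**The case against.** The strongest objection is that the size of the problem rests wholly on an ICC the documents do not give. At zero there is no problem, and at 0.01 it is slight. The programme is 12 weekly sessions of one to two hours against 12 months of follow-up, and the article's background reports limited effects of responsive care on linear growth. A low group ICC for LAZ (Hypothesis 3) is therefore plausible. This stands: the point is conditional, and a reader who infers that every arm 3 contrast must be wrong goes further than the documents allow.

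Four other inferences are tempting and do not hold.

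- Shared neighbourhood as a cause. Groups are formed by residence, but dyads are randomised individually, so resemblance from residence occurs in all arms and is balanced between them. Only correlation created through the groups counts.
- The enrolment cycle missing from the model. Arms are balanced within cycle by blocks of 15. Omitting a balanced blocking factor tends to make standard errors too large, not too small.
- Arm 3 power certainly falling short of 0.36. At ICC 0.01 the detectable effect is 0.354, still below it.
- Biased cost-effectiveness ratios. These use mean effects, which ignoring clustering does not bias. Only their uncertainty is affected.

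Two defences of the plan fail. The cluster-randomised setting in the Sample size section does not cover the groups, because its ICC is serial correlation within a child. Nor is the matter simply left to an analysis plan that is not shown: the article names the levels, considers one further nesting, and passes over the one its own design creates.

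**Conclusion.** The point holds in conditional form. The stated model does not fit the delivery of arm 3. If the group ICC is positive, the arm 3 versus arm 2 and arm 3 versus arm 1 contrasts have standard errors that are too small and a false-positive rate above nominal. The excess is minor at an ICC of 0.01 and material at 0.05. These figures assume 10 equal groups, no group effect in the comparator arm and an alpha of 5% one-sided. If one facilitator leads several groups, there are fewer than 10 effective clusters and the understatement is larger.

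The margin between the stated detectable effect and the 0.36 of Hypothesis 4 is thin: a group ICC of about 0.014 uses it up, if 0.338 is accepted. The egg versus standard care hypotheses and the point estimates of cost-effectiveness are untouched.

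**What to change.** 1. Record parenting group and facilitator for every arm 3 dyad.
2. Prespecify a partially nested mixed model: a group random effect in arm 3 only, with children in arms 1 and 2 as singletons. Place it on the post-baseline arm-by-time effect, on both level and slope. A random intercept alone would not correct a growth-curve contrast, because group effects start after baseline and show mainly in the slopes.
3. Use Satterthwaite or Kenward-Roger degrees of freedom, as there are only about 10 groups.
4. Restate power for the arm 3 contrasts over group ICCs of 0.01 to 0.05, with the significance level stated.
5. Carry the resulting intervals into the arm 3 economic sensitivity analysis.

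The cost is two identifiers, a revised model statement and wider arm 3 intervals: about 5 to 21% wider at ICCs of 0.01 to 0.05, about 40% at 0.10, and slightly more with small-sample degrees of freedom. Neither recruitment nor delivery changes.

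### Arms are balanced within five enrolment cycles, but the stated primary model does not name cycle and no covariate rule guarantees it: a small, avoidable loss of precision

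*Protocol article*

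**What the plan says.** **Design.** The section on recruitment, eligibility and screening states: "There will be five staggered enrollments, where 120 caregiver-infant dyads are recruited in each six-month cycle, with 40 participating dyads in each" arm. The Randomization section gives the mechanism: "The randomization codes are set with 120 subjects randomized into eight blocks and with each block comprising 15 subjects", with five dyads per arm in every block, and "These 120 randomization codes will be used for each of the five enrollment cycles". The overall allocation is to "randomize the caregiver-infant pairs into one of the three study groups in a 1:1:1 ratio, with 200 dyads assigned to each study condition". If each cycle fills, it contains exactly 40 dyads per arm.

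**Analysis.** Under Statistical analyses (Primary and secondary outcomes), the primary model for Aims 1 and 2 is a growth curve fitted by HLM or HGLM. The text discusses nesting, sets aside nesting of children within families, and concludes that "we apply a two-level HLM model that treats time as level 1 and children as level 2". Enrolment cycle is not mentioned as a level or as a fixed effect.

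**Covariates.** The same section gives three routes into the model:
- an open route: "Several variables represented in summary statistics will also be used as covariates in adjusted outcome analyses";
- covariates suggested by the pathways in Fig. 2;
- a screen: "Empirically derived covariates will be included in analyses when a p-value < .1 results from the likelihood ratio test or the Wald test".

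Cycle is neither listed nor ruled out under any of them.

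**The concern.** When allocation is balanced within a grouping factor, the arm means share that factor's variation and it cancels in the difference between arms. A model that omits the factor does not know this. It counts between-group variation as noise and reports a standard error larger than the design earned. The usual remedy is to put the factor in the model because the design used it, whatever its p-value.

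Here the factor is enrolment cycle. The protocol is explicit about the levels of the model and about how covariates enter, yet on the text given cycle may be absent, or may enter for one outcome and not another according to a significance screen. At stake is a little power in the Aim 1 and 2 comparisons and the removal of one data-dependent choice from the primary model. The validity of those comparisons is not at stake.

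**Working it through.** **Inputs from the protocol**
- Five cycles, 120 dyads each, 40 per arm (recruitment section).
- 200 per arm, 600 in total (Randomization).
- Power 0.80 for an effect size of 0.338 at ICC 0.7 (Sample size).
- One-sided superiority testing (Statistical analyses); no numerical alpha is given.

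**Assumptions**
- Alpha 0.05, one-sided, with two-sided as a check.
- r, the share of the variance relevant to the arm contrast that lies between the five cycles. The protocol gives no value, so r = 2%, 5% and 10% are shown.

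**The plan's own figure.** The stated 0.338 (ICC 0.7) and 0.31 (ICC 0.3) could not be reproduced together. With persons as clusters, five waves, two-sided alpha 0.05 and 400 children in a two-arm comparison, (z.975 + z.80) × √[4(ICC + (1 − ICC)/5)/400] gives about 0.245 and 0.186. The software settings are not reported, so this does not show the stated figures to be wrong. The present point does not depend on them; it needs only the planned power of 0.80 as a starting value.

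**Effect of including cycle.** With arms balanced within cycle and a linear model:
- SE with cycle / SE without = √(1 − r)
- Power with cycle, one-sided = Φ[(z.95 + z.80)/√(1 − r) − z.95], where z.95 + z.80 = 1.645 + 0.842 = 2.487
- True one-sided error if cycle is omitted = 1 − Φ[1.645/√(1 − r)]
- Extra dyads the unadjusted analysis would need = 600/(1 − r) − 600

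| Assumed r | SE ratio | Power, one-sided | Power, two-sided | True error of nominal 5% test | Extra dyads |
|---|---|---|---|---|---|
| 2% | 0.990 | 0.807 | 0.808 | 0.048 | 12 |
| 5% | 0.975 | 0.818 | 0.820 | 0.046 | 32 |
| 10% | 0.949 | 0.835 | 0.840 | 0.0415 | 67 |

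Worked line for r = 10%: √0.90 = 0.949; 2.487/0.949 = 2.621; 2.621 − 1.645 = 0.976; Φ(0.976) = 0.835. Extra dyads: 600/0.90 − 600 = 67.

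Taking 0.338 as the unadjusted detectable effect, multiplying by √(1 − r) gives 0.335, 0.329 and 0.321.

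**Simulation check.** Five cycles, 40 per arm per cycle, two arms, one measurement, 20,000 replicates. At r = 10% the one-sided error was 0.042 without cycle and 0.050 with it; two-sided power at an effect of 0.28 was 0.818 and 0.841. At 2% and 5% the differences had the same sign but were small (error 0.044 against 0.046, and 0.044 against 0.047). The Monte Carlo standard error near 0.05 is √(0.05 × 0.95/20,000) = 0.0015, so these two runs confirm direction only.

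**What r means in a growth curve.** A shift in level between cycles goes into the between-child intercept variance and hardly affects an arm-by-time contrast. Differences in slope between cycles do stay in the error of that contrast. So r should be read mainly as the share of slope variation that lies between cycles, which is why the cycle-by-time term matters more than the cycle term alone.

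**The case against.** The strongest reply is that the sentence on two levels describes nesting and is not a list of fixed effects. Cycle could enter through the open covariate route, Fig. 2 is not shown, and a condensed article commonly leaves the exact covariate list to the analysis plan. Much of this stands: a reader might infer that the plan excludes cycle, and the text does not support that. What remains is that none of the stated routes guarantees a factor the design balances on, and the p < .1 rule makes no exception for it.

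A reader might also infer that season distorts the comparison, because successive cycles start six months apart. The protocol gives no enrolment dates and no seasonal pattern in any outcome. If recruitment runs through each six-month cycle, cycle indicators would capture season only crudely. The point should not rest on season.

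A third tempting reading is that a single time trend fitted to cohorts with different curves biases the treatment effect. It does not: every arm has the same mix of cycles, so cohort-specific shapes cancel in the arm contrast.

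Finally, the size rests on an assumed r, and the √(1 − r) formula is for linear models. In an HGLM or a hazard model, adding a prognostic covariate can also change the conditional effect being estimated. Both remarks are right and limit the figures accordingly.

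**Conclusion.** The concern holds as a minor point about precision. The design balances arms within enrolment cycle; the stated analysis neither names cycle nor ensures that it enters. If it is left out, the result is a slightly large standard error and a slightly conservative test, with no bias in the arm contrast and no inflation of type I error.

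The gain from including it is about 1 to 2 power points if cycle terms explain 2% to 5% of the relevant variance, and about 4 points at 10%. These figures assume full cycles at 40:40:40, alpha 0.05 and a linear model, and r has no source in the protocol. If cycles differ in level but hardly in slope, the gain for an arm-by-time contrast is close to nil.

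**What to change.** Add one sentence to the statistical analysis section: in the HLM and HGLM models for Aims 1 and 2, enrolment cycle (four indicators) and cycle-by-time are included as pre-specified fixed effects whatever their significance, and are exempt from the p < .1 rule.

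**Cost.** No new data. With a linear time trend, 4 + 4 = 8 degrees of freedom. With time as a five-level factor for the growth outcomes, 4 + 4 × 4 = 20. Either is small against 600 children.

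Stratifying the proportional hazards models by cycle is optional: the protocol introduces those models under Aim 3, outside the primary hypotheses.

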To prevent data missingness, the field study coordinator will review the data to ensure data completeness prior to weekly data uploads to the secure Research Electronic Data Capture (REDCap) server hosted at Washington University in St. Louis [92]. The coordinator will subsequently follow up with study enumerators responsible for entering a given participant’s data to address quality issues and facilitate follow up with the study participant. Additionally, prior to all data analysis, presence, type, and number of missing observations will be explored. Logistic regression models will determine the type of missingness, whether data are missing at random (MAR), and whether the missingness is monotonic or non-monotonic. To address the possible issues with missing data, multiple imputation techniques [93] will be used to secure robust and unbiased results. Multiple imputation is highly recommended when data are MAR or missing completely at random MCAR [94, 95]. A minimum of 20 imputed files will be generated by using chained equations at the imputation stage. Outcome analysis will be performed on each imputed file, and results are aggregated by applying Rubin’s rule [93].

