#### Economic evaluation

Economic assessments are specifically tied to the study’s fourth aim. To compare the efficiency of the interventions, we will conduct a cost-effectiveness analysis (CEA) to compare arm 2 to arm 1 and arm 3 to arm 2. The difference in effects (E2-E1 or E3-E2) divided by the corresponding cost difference (C2-C1 or C3-C2) constitutes the incremental cost-effectiveness ratio (ICER) [96, 97]. E1 and C1 are treated as zero for standard well-baby care. C2 and C3 are per participant costs of each respective intervention, while E2 and E3 are mean impacts for relevant study outcomes, such as LAZ or ASQ scores. Thus, multiple ICERs are reported, one for each outcome. If the ICER for 3 vs. 2 is less than the ICER for 2 vs. 1, then the costs of the more intensive intervention are offset by improvements in outcomes and arm 3 is an efficient use of resources.

For broader generalizability, we will also aggregate all study outcomes by conducting a basic cost-benefit analysis (CBA) in which non-overlapping outcome changes for arms 2 and 3 are valued in terms of local currency. Several CBA studies on nutrition in Haiti exist [98, 99] and will provide valuation estimates for most of our study outcomes, as well as a benchmark for the efficiency of this study’s intervention relative to other child health interventions in Haiti. For the CBA, B2 and B3 are the sum of all effects (E2 and E3) for the respective study arms, valued in Haitian gourdes. Benefit-cost ratios reflect efficiency (B2/C2, B3/C3), while net differences indicate how much, if any, an arm improves net welfare [(B2-B1)-(C2-C1)] and [(B3-B2)-(C3-C2)].

For both types of economic evaluation, we will conduct sensitivity analysis of the estimates using both simple 1-way (min/max) and Monte Carlo (multi-way, probabilistic) approaches to reflect statistical confidence intervals in study impacts and costs. In the CEA, costs and effects are measured in a single year, but in the CBA, benefits include a “stream” of gains (estimated into the future) and must be discounted following standard guidelines of 3-12% [96, 97, 99], a factor also included the sensitivity analysis.

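### The missing-data plan treats MAR as something logistic regression can establish and calls the imputed results unbiased, but MAR can only be assumed

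*Protocol article*

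**What the plan says.** The missing-data paragraph sits in the protocol article under Statistical analyses, Primary and secondary outcomes. After describing data-quality checks and an exploration of what is missing, it says "Logistic regression models will determine the type of missingness, whether data are missing at random (MAR". The same sentence also gives these models the task of classifying the missingness as monotone or not.

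It then says that "multiple imputation techniques [93] will be used to secure robust and unbiased results", and adds: "Multiple imputation is highly recommended when data are MAR or missing completely at random MCAR [94, 95". The method follows: "A minimum of 20 imputed files will be generated by using chained equations at the imputation stage", pooled by Rubin's rule.

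Two other statements in the same subsection bear on the point: "all analyses will follow an intention-to-treat framework" and "all hypothesis testing will be based on a one-sided superiority paradigm". The paragraph names no step for data that are not MAR. The only sensitivity analysis in the article belongs to the economic evaluation: "For both types of economic evaluation, we will conduct sensitivity analysis of the estimates".

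**The concern.** The difference between MAR and MNAR is whether, given everything observed, the chance of being missing still depends on the value that was not seen. A logistic model fitted to observed variables contains no information on that. It can find predictors of loss, which is evidence against MCAR and a good way to pick auxiliary variables for the imputation model. A clear set of predictors is equally compatible with MAR and with MNAR.

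The text therefore credits a diagnostic with a conclusion it cannot reach, and the next sentence credits imputation with a property it has only if that conclusion is true. At stake is how the primary results on growth and development are described: as free of bias from loss to follow-up, when they are valid only under an assumption.

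Informative loss is not far-fetched here. Arms 2 and 3 have a weekly egg ration with log collection, arm 3 also has weekly group sessions of one to two hours, and arm 1 has neither (Egg intervention; Parenting intervention). An intention-to-treat analysis of all randomised children relies on imputed values for those who are lost.

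**Working it through.** The paragraph states no figure to reproduce, so the check asks two things: can the diagnostic tell MAR from MNAR, and how large could the bias be?

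**1. Can the diagnostic tell them apart?**

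From the document: 200 children per arm (Randomization: "with 200 dyads assigned to each study condition"), at least 20 imputations, Rubin's rule, one-sided testing. Assumed, because the article does not give them: true effect 0, baseline–endline correlation 0.7, about 14% missing in each arm, one-sided alpha 0.05, 1,000 simulated trials per scenario. Loss depended on baseline in every scenario. In the two MNAR scenarios, loss in one arm also depended on the unseen endline residual, with worse children more likely to be lost. The logistic model regressed missingness on arm and baseline.

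| Scenario | Missing, two arms | Logit coefficient: arm / baseline | Arm term p<.05 | Imputed estimate of a true 0 (SD) | One-sided 5% rejection |
|---|---|---|---|---|---|
| MAR | 14.0% / 13.9% | -0.02 / -0.31 | 4% | 0.000 | 5.7% |
| Moderate MNAR | 14.1% / 13.8% | -0.03 / -0.31 | 5% | 0.047 | 16.2% |
| Stronger MNAR | 13.9% / 13.8% | -0.01 / -0.28 | 5% | 0.085 | 29.8% |

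The logistic output is practically the same in all three rows, while the imputed estimate goes from correct to clearly biased. Loss rates were equal between arms, so comparing them would not have revealed the problem either.

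**2. How large could the bias be?**

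Let p be the share missing in an arm, and delta the amount by which the unseen children fall below their MAR prediction. Imputation under MAR overstates that arm's mean by p × delta, so

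bias in (intervention − control) = p_int × delta_int − p_ctl × delta_ctl.

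As a cross-check on the simulation, where only one arm was affected: 0.047 / 0.138 = 0.34 SD and 0.085 / 0.138 = 0.62 SD are the deltas those two scenarios imply.

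With the same delta in both arms, the size is |p_int − p_ctl| × delta:

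- 10 v 20% missing, delta 0.3: 0.10 × 0.3 = 0.03 SD
- 10 v 20% missing, delta 0.5: 0.10 × 0.5 = 0.05 SD
- 5 v 20% missing, delta 0.5: 0.15 × 0.5 = 0.075 SD

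Taking 1 LAZ as about 1 SD, against the 0.30 LAZ of Hypothesis 1 (Table 1): 0.03 / 0.30 = 10%, 0.05 / 0.30 = 17%, 0.075 / 0.30 = 25%.

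**3. Direction.** If control loses more (20 v 10%, delta 0.5), the bias is 0.10 × 0.5 − 0.20 × 0.5 = −0.05 SD, against the intervention. Swap the loss rates and it is +0.05 SD, in its favour.

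**The case against.** The best defence is that this is loose wording with little effect on the analysis. Imputation is planned whatever the logistic models show, and the sentence after the claim ties imputation to MAR or MCAR. Both points are true. A reader might infer a decision rule in which a significant predictor certifies MAR, but the text sets no threshold and makes nothing depend on the result. The qualifying sentence softens the word unbiased, yet it leaves standing the statement that the data can settle whether MAR holds.

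A reader might also infer that MNAR loss will go unexamined. The document does not support that. This is a condensed article, the SAP is not shown, and a missing-data sensitivity analysis is commonly placed there. Its absence here is no fault. An SAP could add such an analysis, but it would not make the published sentence correct.

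On size, a reader might set the same biases against the 0.10 LAZ of Hypothesis 3 and get 30–75%. That comparison is poorly matched: Hypothesis 3 compares arm 3 with arm 2, both of which have weekly egg contact, so only the group sessions differ. Nothing in the article suggests a gap such as 5 v 20% between them.

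The deltas are also not small. If serial measurements have equal correlation at the 0.7 used in Sample size, the residual SD is √(1 − 0.49) = 0.71 given baseline, and √(1 − 4 × 0.49 / 3.1) = 0.61 given four earlier waves. A delta of 0.5 SD is then about 0.7 to 0.8 residual SDs. The simulation conditioned on baseline only and built in one-arm MNAR, so it shows what is possible, not what is likely.

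Finally, all arms share the follow-up schedule, all participants are compensated for assessments, and data completeness is reviewed weekly. These features reduce the risk of differential loss without removing it.

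**Conclusion.** The point holds as a wrong statement about method. The plan says observed data will determine whether MAR holds, and says imputation will give unbiased results. The first is not possible and the second is conditional on an assumption that cannot be tested. MAR would be presented as established when it is only assumed, which affects what the trial may conclude.

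The size is illustrative only. A bias of 0.03 to 0.075 SD, about 10–25% of the Hypothesis 1 effect, rests on assumed loss differences of 10 to 15 points, an assumed delta of 0.3 to 0.5 SD that is equal in both arms, and 1 LAZ being about 1 SD. It should not be read as a forecast.

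Nor should it be read as bias in favour of the intervention. If the control arm, with less contact, loses more children and those children are doing worse, the bias runs against the intervention. Under one-sided testing only bias in the favourable direction inflates false positives.

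**What to change.** Rewrite the missing-data paragraph along these lines:

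- State that MAR is an assumption of the main analysis and is not tested.
- Use the logistic models only to describe predictors of missingness and to choose auxiliary variables for the chained equations.
- Replace the claim of unbiased results with a statement that the results are valid under MAR.
- Unless the SAP already does this, re-run the planned imputations with delta shifts that vary by arm, in the unfavourable direction, for LAZ and the ASQ domains. Report the shift at which each primary conclusion changes. A range of 0 to 0.5 SD would be one reasonable start, widened if no change of conclusion falls inside it.

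The cost is a change of wording and some extra computing on imputations already planned. No new data are needed. The drawbacks are a little more analysis to report and a less favourable description of the main results.
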